## Methods

### Study design

This protocol is for a single arm, non-randomized, controlled trial (Fig. 2) reported in accordance with the SPIRIT statement. This design will ensure that factors, such as gut flora, digestion and other physiological variables, which could influence the study results, remain consistent in participants throughout the study period, as the same group of participants will serve as both the control and test groups. This consistency will enable reasonable comparisons with minimum effect due to individual differences. A wash-out period is not considered in the design, as *diyabath* is introduced as the intervention only after the initial control phase.

**Fig. 2 Fig2:**
[figure not shown]
Flow diagram of the trial

### Study setting

Participants for the study will be recruited from a women’s hostel located in Colombo District. This area is popular among young adults engaged in education and employment due to its proximity to several universities and workplaces within a 5 km radius. The hostel residents, women aged 20–35 years who have moved to this area for work or study, consume all three meals prepared daily in the hostel. By selecting this setting, it ensures consistent food intake across all participants and represents the population of apparently healthy young women of reproductive age in Sri Lanka.

### Study population

Women aged 20–35 years who have been residing in Colombo District for a minimum period of two years and with normal body mass index (BMI) (18.5 to 24.9kg/m^2^) will be recruited.

Pregnant and lactating women; those on long term medication for metabolic illnesses, severe concurrent infections, bowel disorders or intolerance to cereal based foods, coconut milk, red onion and dried chili (diagnosed following a clinical assessment made by a medical practitioner along with perusal of diagnosis cards, clinic records and treatment prescriptions for confirmation); women already consuming *diyabath* or any nutritional supplementation; or on antibiotics at the time of the study or within past two weeks will be excluded from the study.

### Intervention

The intervention consisted of a pre-determined portion of *diyabath* (1 cup or 230 g) measured and served in standardized containers, on every alternate day (week days only) during the 10 weeks of intervention period.

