**Methods:**

This is a single arm, non-randomized controlled trial among 45 women aged 20–35 years, purposively selected from a residential hostel in Colombo District, Sri Lanka. The primary outcomes: gut microbiome composition, nutritional status, and health and immune markers will be assessed before and after a 10-week control phase, during which participants will follow their usual dietary habits (control). In the subsequent 10-week intervention phase, the same participants will consume *diyabath* daily as a pre-breakfast meal (intervention). The *diyabath* will be prepared according to an optimal recipe identified through a comprehensive evaluation of traditional recipes during the intervention development phase. Outcomes will be reassessed immediately and one month after completing the intervention. Changes in outcomes between the control and intervention phases will be compared.

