### Outcomes

Outcomes will be measured at four time points: at the baseline (T_0_), after completion of the 10-week non-intervention control period (T_1_), after completion of the 10-week intervention period (T_2_) and 4 weeks after completion of the intervention (T_3_) (Fig. 3).

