**Fig. 4 Fig4:**
[figure not shown]
CONSORT flow chart for the trial

**Table 1 Tab1:** Participant timeline

Task	Study period (weeks)													
	**Recruitment**	**Non-intervention control period**						**Intervention period**					**Post-intervention follow up**	
ENROLLMENT - Eligibility screening - Informed consent	−2	0^a^	2	4	6	8	10^b^	12	14	16	18	20^b^	21	22^b^
	X													
	X													
Maintaining a food diary (24 h dietary records)		x	x	x	x	x	x	x	x	x	x	x	x	x
Baseline control assessment		x												
Anthropometry (height, weight, Waist circumference, Hip circumference, BMI)		x					x					x		x
Collection of blood samples (fasting) - serum micronutrients & serum ferritin - serum lipid profile - serum free fatty acids - AST, ALT - hsCRP, IL-6, IL-10, Cytokines - FBS & serum insulin		x					x					x		x
Collection of stool samples - Gut microbiome analysis (% abundance, alpha-diversity index, F/B ratio) - Short chain fatty acid profile		x					x					x		x

^a^assessment is done at the beginning of the week

^b^assessment is done at the last day of the week

Participants will be informed not to take part in any other nutritional intervention as well as not consume any nutritional supplementations including other cooked rice-based fermented foods during the study. A list of such food items will be given to them for reference at the beginning of the study. In addition, each participant will be asked to record daily all the foods that they have eaten other than what is provided by the hostel throughout the intervention phase. These records will be checked by an investigator during weekdays. Set reminders will be sent daily via SMS to all participants to keep records of their diets and will be asked to acknowledge the receipt of the message.

During the intervention period, every morning, the participants will be reminded via SMS to be present at the breakfast table. Standard portions of *diyabath* will be placed in the dining area before breakfast, ensuring uniformity in presentation across all participants. One investigator will be present at the site to observe the participants, to ensure that they consume *diyabath* as intended and answer any queries. The participants are requested to finish the served amounts and return the containers. If there is any leftover *diyabath*, the investigator will weigh it and make a record of it. This procedure will be repeated daily for 10 weeks during the intervention phase.

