#### Compliance and drop-outs

Based on the total amount of *diyabath* consumed throughout the intervention, as per the records, participants whose compliance with the consumption of *diyabath* is ≤ 70% of the total dose will be considered as dropped-out.

To enhance compliance, the participants will be briefed on the importance of continuing with the study and the potential health benefits. They will be informed that they will receive their test results with regards to biochemistry and body anthropometry, which will be an incentive to remain in the study.

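### The serving schedule is daily in the Abstract and Implementation text but alternate weekdays in the Intervention section, so the total dose and the 70% compliance cut-off are not fixed

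*Protocol article*

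**What the plan says.** Four places in the protocol article bear on how often diyabath is eaten.

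- **Abstract, Methods:** "the same participants will consume *diyabath* daily as a pre-breakfast meal (intervention").
- **Intervention:** the intervention is "a pre-determined portion of *diyabath* (1 cup or 230 g) measured and served in standardized containers", served "on every alternate day (week days only) during the 10 weeks of intervention period".
- **Implementation, on reminders:** "During the intervention period, every morning, the participants will be reminded via SMS to be present at the breakfast table".
- **Implementation, on placing portions, observing intake and weighing leftovers:** "This procedure will be repeated daily for 10 weeks during the intervention phase".

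Compliance and drop-outs then sets an adherence rule on the total amount eaten. Participants at or below 70% "of the total dose will be considered as dropped-out". No section states the total dose or the number of planned servings, and Table 1 has no row for servings. Statistical analysis limits the per-protocol population to women who adhered completely to the protocol.

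**The concern.** The section that defines the intervention gives one frequency, and the sections that summarise it and describe its delivery give another. All of this is current text. It is a conflict between statements that the article does make, so a fuller document left unshown would not explain it.

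Two things are at stake.

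1. **The exposure being tested.** Background argues for diyabath from its nutrient content per serving, for example up to 15% of the daily recommended value of iron, and serum ferritin and micronutrients are among the primary outcomes. A positive or null result cannot be read, replicated or promoted without knowing how many servings it refers to, and it could be reported for a dose the women did not receive.
2. **Who counts as compliant.** The drop-out rule is a percentage of an unstated total, so its denominator changes with the schedule. Complete adherence, which defines the per-protocol population, also cannot be judged against two incompatible schedules.

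**Working it through.** The article prints no total dose, so there is no stated figure to reproduce.

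**Inputs.** Portion 230 g (Intervention); duration 10 weeks, which is 70 days (Outcomes); cut-off at or below 70% of total dose (Compliance and drop-outs); frequency as quoted above.

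**Formulas.** Servings = servings per week × 10. Total dose = servings × 0.23 kg. Cut-off = 0.70 × servings.

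Both phrases allow more than one reading. Daily may mean seven days or weekdays only. Alternate weekdays may mean Monday, Wednesday and Friday (3 × 10 = 30). It may also mean strict alternation with weekends skipped: each 14-day cycle has 7 alternate days, 5 of them weekdays, and 5 cycles give 25. Taking every second weekday gives the same count, 50 / 2 = 25.

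| Reading | Servings | Total dose | 70% cut-off |
|---|---|---|---|
| Daily, seven days | 70 | 16.1 kg | 49 servings (11.27 kg) |
| Daily, weekdays only | 50 | 11.5 kg | 35 servings (8.05 kg) |
| Monday, Wednesday, Friday | 30 | 6.9 kg | 21 servings (4.83 kg) |
| Strict alternation, weekends skipped | 25 | 5.75 kg | 17.5 servings (4.03 kg) |

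**Dose ratios.**
- Seven-day daily against alternate weekdays: 70/30 = 2.33 to 70/25 = 2.80.
- Weekday daily against alternate weekdays: 50/30 = 1.67 to 50/25 = 2.00.

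**Effect on the 70% rule if serving and scoring follow different schedules.**
- Served on alternate weekdays, scored against seven-day daily: a woman who eats everything reaches 25/70 = 35.7% to 30/70 = 42.9%. Against weekday daily she reaches 25/50 = 50% to 30/50 = 60%. Under either reading of daily, every fully compliant woman is classed as dropped out.
- Served daily for seven days, scored against 30 servings: a woman who eats 22 portions passes the cut-off of 21, though she has eaten only 22/70 = 31% of what was served.

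**Effect on the nutrient argument.** Up to 15% of the daily iron value per serving stays up to 15% per calendar day on a seven-day schedule. Averaged over all calendar days on alternate weekdays, it falls to between 15 × 25/70 = 5.4% and 15 × 30/70 = 6.4%.

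**The case against.** The best reply is that daily means each serving day, and that the Intervention section, as the defining text, governs. The seven-day reading is also not certain. The Intervention section confines serving to weekdays and the Implementation section has diet records checked on weekdays, so the largest ratios may overstate the gap. The reminder text concerns attendance at breakfast and does not itself state a serving frequency.

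On compliance, intake is observed and leftovers are weighed. The natural denominator is therefore what was scheduled, and actual intake should be recoverable afterwards. The mass drop-out result needs the team to serve on one schedule and score on another, which the article does not say it will do. Neither the sample size nor the t-tests depend on serving frequency.

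Part of this stands. The weekday reading lowers the ratio to between 1.67 and 2.00, the mass drop-out result is a conditional worst case, and the compliance problem disappears once the schedule is settled. None of it removes the contradiction. Nothing in the article restricts daily to serving days, and that gloss fits poorly with reminders every morning and a routine repeated daily for 10 weeks. Alternate weekdays conflict with either reading of daily. Weighed leftovers help to report what was eaten, but they do not fix in advance which exposure is under test.

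**Conclusion.** The concern holds. The article gives two incompatible serving schedules. On the plain seven-day reading of daily, the planned total dose differs by a factor of 2.3 to 2.8 between them; if daily is confined to weekdays, the factor is 1.7 to 2.0. The 70% cut-off cannot be computed from the article and ranges from 17.5 to 49 servings.

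These figures assume a constant 230 g portion and a full 70-day intervention phase with no missed days. The internal before-and-after comparisons remain computable if every woman follows one schedule. The damage is to what exposure the result describes and to who is counted as compliant, dropped out or per-protocol. Because the exposure itself is not fixed, this must be corrected.

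**What to change.** 1. Reconcile the Abstract, Intervention and Implementation texts to a single schedule, and state the planned number of servings. The choice belongs to the investigators.
2. In Compliance and drop-outs, define total dose as the number of scheduled servings under that schedule times 230 g, and compute the 70% rule on that denominator.
3. Align the reminder, observation and leftover-weighing text with the same schedule, so that complete adherence for the per-protocol population can be judged.

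This should be done before the intervention phase starts. The article does not give recruitment status. If the phase has already begun, the schedule actually delivered should be documented and used as the denominator.

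The cost is protocol wording plus notification of the ethics committee and the registry; the article already commits to notifying the registry of amendments. No extra participants, visits or samples are needed.

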### Outcomes

Outcomes will be measured at four time points: at the baseline (T_0_), after completion of the 10-week non-intervention control period (T_1_), after completion of the 10-week intervention period (T_2_) and 4 weeks after completion of the intervention (T_3_) (Fig. 3).

**Fig. 3 Fig3:**
[figure not shown]
Time structure of the trial

Primary outcomes of the study include changes in the following parameters:*Host gut microbiome composition:* Evaluated using percentage abundance of probiotic strains (i.e. *Lactobacillus* spp, *Bifidobacterium* spp) and other beneficial microorganisms (i.e. *Oscilllospira*, *Akkermansia muciniphila*), alpha-diversity index and firmicutes-to-bacteroidetes ratio (F/B). Diversity index reveals the change in the gut microbiome composition and is important to have a balanced ratio between the most common two phyla (Firmicutes and Bacteroidetes F/B) for homeostasis of the gut [38]. Gut microbiota is directly responsible to develop digestive, immunological and metabolic functions in host [39, 40].*Nutritional status and health parameters*: Evaluated by serum micronutrients and serum ferritin*Health biomarkers*: Assessed by lipid profile, high-sensitivity C-reactive protein (hsCRP), fasting blood sugar (FBS), aspartate aminotransferase (AST), alanine aminotransferase (ALT) and serum insulin*Immune markers:* Evaluated by analysing interleukin-6 (IL-6), IL-10 and cytokines

Each participant is expected to improve these parameters to either reach a healthy limit or a healthier end if already in the healthy limit.

Secondary outcomes of the study include:*Antioxidant capacity:* An increase in total antioxidant capacity in serum after consumption of an antioxidant rich food indicates absorption of antioxidants from the food and an enhanced in vivo defence status against oxidative stress [41].*Anthropometry:* Measured as waist circumference, hip circumference and BMI

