#### Biochemical assessments

A venous blood sample of 10 ml will be drawn from each participant under aseptic conditions after an overnight fast (12 h). This will be done at the hostel premises, while half of the blood volume will be centrifuged within one hour, and the serum/plasma separated, aliquoted and kept frozen at − 20 °C until further analysis. The remaining blood will also be stored as whole blood. The samples will be analysed as given below at the Faculty of Medicine, University of Colombo, Sri Lanka.*Micronutrients:* Serum Folate, Vitamin D and serum ferritin using the MAGLUMI® chemiluminescence immunoassay (CLIA) and serum calcium level using commercially available kits*Health and immune biomarkers:* Serum lipid profile, FBS, AST, and ALT using commercially available kits, and hsCRP, serum insulin and immune markers (IL-6, IL-10) using the MAGLUMI® chemiluminescence immunoassay (CLIA).

Further, antioxidant capacity will be analysed using colorimetric ABTS method at the Industrial Technology Institute, Sri Lanka [52].

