### Statistical analysis

Data will be analysed using the statistical package for the for the Social Sciences (SPSS) version 21.0. The changes in nutritional, health and immune parameters between the baseline (T_0_) and at the end of control phase (T_1_) will be analysed first to identify any significant change with time. The end point of control phase will serve as the pre-intervention point for further assessments. The changes in outcomes between the pre-intervention point (T_1_) and at the end of intervention phase (T_2_) will be analysed to determine any significant effects of *diyabath* consumption on the study group.

Paired t-test will be performed to determine the significance of the mean difference of pre- and post- measurements during the intervention phase. *P* value less than 0.05 is considered statistically significant.$$\begin{aligned} {\mathrm H}_0=\:&\left[\mathrm{Pre}-\mathrm{intervention}\;\mathrm{measurements} -\mathrm{post}\right. \left.-\:\mathrm{intervention}\;\mathrm{measurements}\right]=0 \end{aligned}$$

The same analysis will be performed in relation to the control phase. This evaluation is important to reveal any possible change in parameters that can occur due to seasonal, physiological or climatic changes in individuals.

Further, independent sample t-test will be performed to assess the significance between the intervention and control phases, in relation to the mean change in pre- and post-measurements observed during the intervention and control phases.$$\begin{aligned} {\mathrm H}_0=\:&\left[\mathrm{Mean}\;\mathrm{change}\;\mathrm{in}\;\mathrm{control}\;\mathrm{phase} \right. \left. -\:\mathrm{Mean}\;\mathrm{change}\;\mathrm{in}\;\mathrm{intervention}\;\mathrm{phase}\right]=0 \end{aligned}$$

Bioinformatics analysis of metagenomics of microorganisms evaluated from stool samples will be carried out based on16S amplicon sequence variants (ASVs) model.

Analysis of the effect of diyabath on primary outcomes will be based on modified intention-to-treat (mITT) and per-protocol (PP) principles. The mITT population will include participants who completed the first 15 weeks of the study period which covers the control phase and half of the intervention phase. The PP population will include the participants who completely adhered to the study protocol [53]. Missing data will be adjusted with multiple imputation.

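### At least 18 variables are labelled primary and tested at an unadjusted 0.05, and the plan does not say whether the T1–T2 test or the between-phase test decides

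*Protocol article*

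**What the plan says.** The Outcomes section introduces its first list with "Primary outcomes of the study include changes in the following parameters". Four domains follow: gut microbiome, nutritional status, health biomarkers and immune markers. The microbiome domain is "Evaluated using percentage abundance of probiotic strains" and other beneficial organisms (four taxa named in all), plus alpha-diversity and the Firmicutes-to-Bacteroidetes (F/B) ratio. The nutritional domain is "Evaluated by serum micronutrients and serum ferritin". Biochemical assessments itemises it as "Serum Folate, Vitamin D and serum ferritin using the MAGLUMI" immunoassay, and "serum calcium level using commercially available kits". A separate secondary list holds only antioxidant capacity and anthropometry. The Abstract also presents all the main domains as primary.

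Statistical analysis sets one threshold: a P "value less than 0.05 is considered statistically significant". It describes three comparisons:
- a paired t-test of T1 against T2, where the changes "will be analysed to determine any significant effects of" diyabath;
- the same paired test of T0 against T1, to reveal seasonal, physiological or climatic change;
- an independent-samples t-test of the mean change in the intervention phase against that in the control phase.

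The section does not rank the first comparison against the third. It does not say how many primary outcomes, or which, must reach significance. The Sample size section uses one microbiome variable, the presence of *Oscillospira*, at T1 and T2.

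**The concern.** The protocol does rank its outcomes, since it has a secondary list, but it leaves at least 18 variables at the top. Each is held to the threshold suited to a single primary outcome. The calculation behind the 45 participants likewise assumes one variable tested once at 0.05.

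Two separate errors can follow. First, with this many unadjusted tests, one or more significant primary results can be expected often by chance alone. Second, the test that the text links to the effect of diyabath is a before-after comparison with no control. The 10-week control phase exists to show what happens without diyabath, and only the between-phase comparison uses it for that purpose. If a parameter changes with season or hostel menu, T1–T2 alone will credit the change to the food.

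The Discussion says the programme will be promoted in the community if outcomes are successful, and does not define success. A result produced by chance or drift could therefore feed into public advice.

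**Working it through.** **Count of primary variables**

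| Domain | Variables | Number |
|---|---|---|
| Microbiome | *Lactobacillus*, *Bifidobacterium*, *Oscillospira*, *Akkermansia*; alpha-diversity; F/B | 6 |
| Nutritional | folate, vitamin D, calcium, ferritin | 4 |
| Health | lipid profile (counted as one), hsCRP, FBS, AST, ALT, insulin | 6 |
| Immune | IL-6, IL-10 (unspecified cytokines left out) | 2 |
| Total | | 18 |

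If the lipid profile is assumed to have four components, the total is 21.

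**The plan's own figure.** With p1 = 31, p2 = 73 and f = 7.9: (31×69 + 73×27) × 7.9 / 42² = 4110 × 7.9 / 1764 = 18.41. Doubling gives 36.8, and adding 25% gives 46.0, against 45 stated. The published size is reproduced to within one participant. It rests on one dichotomous variable and one test. The protocol states no overall error rate across its primary outcomes.

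**Chance of at least one false significant primary result.** Assumptions: no true effect, no drift, one correctly sized two-sided test per outcome. (The protocol does not state sidedness.)
- Independent, any direction: 1 − 0.95^18 = 0.603; for 21 outcomes, 1 − 0.95^21 = 0.659.
- Independent, favourable direction: 1 − 0.975^18 = 0.366.
- Correlated: equal pairwise correlation between normal test statistics. The protocol gives no correlations, so a range is shown.

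| 18 outcomes, one test each | r = 0 | 0.3 | 0.5 | 0.7 |
|---|---|---|---|---|
| Any direction | 60% | 51% | 40% | 28% |
| Favourable direction only | 37% | 26% | 20% | 14% |

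One pre-named outcome with one test would give 5% and 2.5%.

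**If either T1–T2 or the between-phase test may count.** This was simulated with 8,000 null trials per setting, 36 women and independent within-woman errors (both assumed), using the independent-samples test as planned.

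| 18 outcomes, either test | r = 0 | 0.3 | 0.5 | 0.7 |
|---|---|---|---|---|
| Any direction | 90% | 84% | 72% | 54% |
| Favourable direction only | 67% | 48% | 37% | 28% |

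Part of this rise comes from the independent-samples test. Both changes come from the same women and share T1, so under these assumptions its size per outcome is about 11%. A paired analysis of the two changes holds 5%.

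**Drift read as effect.** Suppose diyabath does nothing but the parameter drifts between T1 and T2 by δ standard deviations of the paired change. The paired t-test then has noncentrality δ√n. The drift values are assumptions. The range of n runs from 45 × 0.75 ≈ 34 (all of the 25% allowance lost) to 45.

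| Drift δ | Significant, n = 34 | Significant, n = 45 |
|---|---|---|
| 0.1 | 9% | 10% |
| 0.2 | 20% | 26% |
| 0.3 | 40% | 50% |

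These are rates per outcome. Multiplicity adjustment would make them smaller but would not remove the bias.

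**The case against.** Several points on the other side are fair.

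*Multiplicity procedures usually sit in the analysis plan, which is not shown.* This stands, so the absence of a named adjustment is not the charge. The protocol itself fixes the primary label, the threshold and the tests, and an adjustment written elsewhere would have to contradict or supplement that text.

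*The plan does deal with drift.* In part it does. It tests T0–T1 and compares the changes between phases, and the Abstract names that comparison. The drift table therefore describes T1–T2 read alone. The difficulty is that Statistical analysis attaches the diyabath effect to T1–T2 and gives the between-phase test no precedence.

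*There are three tests per outcome.* A reader might multiply the error by three. The T0–T1 test looks for change over time and cannot support a claim for diyabath, so at most two tests bear on benefit.

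*A false claim of benefit is more likely than not.* A reader might infer this from the 60%, but the documents do not support it. The 60% needs independent outcomes and counts significant worsening too. In the favourable direction one test per outcome gives 37% at most for 18 outcomes. For 18 outcomes the favourable figure passes 50% only if either test may count and outcomes are nearly uncorrelated (67% at correlation 0, 48% at 0.3). F/B is described only as needing balance, so a change either way might be called favourable. That raises the favourable figure somewhat but does not establish the stronger statement.

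*Any single significant outcome would trigger promotion.* The Discussion speaks of successful outcomes in general and states no such rule. The gap is that no rule is given.

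**Conclusion.** The concern holds in a limited form. At least 18 variables share primary status at an unadjusted 0.05, and neither of the two tests that bear on benefit is declared decisive. With one test per outcome, the chance of at least one false significant primary result lies between about 28% and 60% over assumed correlations from 0.7 down to 0. In the favourable direction it lies between about 14% and 37%. Even 14% is more than five times the 2.5% of a single pre-named test. The figures are higher if either test may count. They rest on equal pairwise correlations, which the protocol does not give, and on counting the lipid profile as one variable and the open-ended cytokines as none.

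The drift problem is separate. T1–T2 alone is significant in about 9–10%, 20–26% or 40–50% of cases per outcome at assumed drifts of 0.1, 0.2 or 0.3 SD of the paired change. The documents give no estimate of actual drift, so these rates show sensitivity and do not predict what will happen.

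**What to change.** Before T2 results are seen, amend the protocol, the analysis plan and the registry entry as follows.

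1. Name one primary outcome from the microbiome domain, which already drives the sample size. State whether it is the presence of *Oscillospira*, as in Sample size, or its percentage abundance, as in Outcomes. These are different variables, one dichotomous and one continuous, and they need different analyses.
2. Name the within-woman between-phase contrast, (T2 − T1) − (T1 − T0), analysed as paired data, as the decisive test.
3. Make the other listed outcomes secondary, with Holm or Benjamini-Hochberg adjustment, and list the cytokines. If all 18 must stay primary, Bonferroni would require P < 0.05/18 = 0.0028 for each.
4. Label the separate T0–T1 and T1–T2 tests descriptive.

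The cost is more than wording. Fewer outcomes can be called primary findings, and the decisive contrast is not the one that was sized. With independent within-woman errors of variance σ², T2 − 2T1 + T0 has variance 6σ² against 2σ² for T2 − T1, so its standard error is √3 ≈ 1.7 times larger. Correlated errors would change that ratio. The power of 45 participants should be rechecked and restated for this contrast and the chosen outcome.
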